# EnGraft: a multicentre, open-label, randomised, two-arm, superiority study protocol to assess bioavailability and practicability of Envarsus® versus Advagraf™ in liver transplant recipients

**DOI:** 10.1186/s13063-023-07344-7

**Published:** 2023-05-11

**Keywords:** EnGraft, Envarsus, Liver transplantation, Superiority study, Randomised controlled trial

## Abstract

**Background:**

Graft rejection and chronic CNI toxicity remain obstacles to organ transplant success. Current formulations of tacrolimus, such as Prograf® and Advagraf™, exhibit limitations in terms of pharmacokinetics and tolerability, related in part to suboptimal bioavailability. As dosing non-compliance can result in graft rejection, the once daily formulation of tacrolimus, Advagraf™, was developed (vs 2x/day Prograf®). Benefits of Advagraf™ are counterbalanced by delayed achievement of therapeutic trough levels and need for up to 50% higher doses to maintain Prograf®-equivalent troughs. Envarsus® is also a prolonged-release once-daily tacrolimus formulation, developed using MeltDose™ drug-delivery technology to increase drug bioavailability; improved bioavailability results in low patient drug absorption variability and less pronounced peak-to-trough fluctuations. In phase III de novo kidney transplant studies, Envarsus® proved non-inferior to twice-daily tacrolimus; however, no phase IV studies show superiority of Envarsus® vs Advagraf™ in de novo liver transplant (LTx) recipients.

**Methods:**

The EnGraft compares bioavailability and tests superiority of Envarsus® (test arm) versus Advagraf™ (comparator arm) in de novo LTx recipients. A total of 268 patients from 15 German transplant centres will be randomised 1:1 within 14 days post-LTx. The primary endpoint is dose-normalised trough level (C/D ratio) measured 12 weeks after randomisation. Secondary endpoints include the number of dose adjustments, time to reach first defined trough level and incidence of graft rejections. Additionally, clinical and laboratory parameters will be assessed over a 3-year period.

**Discussion:**

C/D ratio is an estimate for tacrolimus bioavailability. Improving bioavailability and increasing C/D ratio using Envarsus could reduce renal dysfunction and other tacrolimus-related toxicities; previous trials have shown that a higher C/D ratio (i.e. slower tacrolimus metabolism) is not only associated with improved renal function but also linked to reduced neurotoxic side effects. A higher C/D ratio could improve clinical outcomes for LTx recipients; EnGraft has begun, with one third of patients recruited by January 2022.

**Trial registration:**

This trial has been registered (4 May 2020) in the EU Clinical Trials Register, EudraCT-Nummer: 2020–000796-20. Additionally, this trial has been registered (22 January 2021) at ClinicalTrials.gov: NCT04720326. The trial received a favourable opinion from the concerned lead ethics committee at the University of Regensburg, under the reference 20–1842-112.

## Background

Liver transplantation (LTx) is the treatment of choice for patients with end-stage liver disease. The liver is the second most frequently transplanted organ with a transplantation rate of 5500 livers per year in Europe [1].

Since the first experimental LTx in 1963, survival rates have improved significantly. This trend can be attributed to improved surgical techniques, donor organ preservation methods and, in particular, to the development and improvement of immunosuppressive medication [2]. The current 1-year post-transplant survival rates for patient and graft in LTx programs are approximately 85% and 80%, respectively; 5-year survival rates for most organ transplant programs range from 50 to 70% [1].

Despite major advances in transplantation medicine, graft rejection remains the key obstacle to long-term success. In clinical practice, a combination of two or three immunosuppressants is normally used to control the immune response in the immediate post-LTx period; this multi-drug regimen typically involves a combination of glucocorticoid (e.g. prednisone), calcineurin inhibitor (CNI) (cyclosporine or tacrolimus) and anti-proliferative agent (e.g. mycophenolate mofetil, azathioprine or everolimus). Other therapeutic agents include interleukin-2 receptor antagonists, such as basiliximab, often used as induction therapy to delay or reduce the need for CNIs. Once graft function has stabilised and the early immune response is controlled, the number and dose of immunosuppressive medications may be gradually reduced to minimise the wide range of overlapping adverse effects that include increased susceptibility to opportunistic infection and increased risk of malignancy.

Therefore, effective immunosuppressive strategies must strike a balance between suppressing the immune response against the transplanted organ whilst simultaneously minimising toxic side effects of the pharmacological interventions. Furthermore, side effects of the immunosuppressive therapy may affect patient compliance with the drug regimen, which is vital for maintaining immunosuppression and therefore assuring graft survival.

Tacrolimus, a macrolide CNI, was introduced to transplant practice in the early 1990s and since then has become the first-line immunosuppressive medication in most LTx programs [1, 3].

Currently marketed formulations of tacrolimus, such as Prograf® and Advagraf™, exhibit limitations primarily in terms of pharmacokinetic properties and tolerability. Tacrolimus has a narrow therapeutic index; blood trough level concentrations between 3 and 15 ng/ml are recommended during the first year after transplantation, provided that tacrolimus is given in combination with mycophenolate, steroids and induction with an anti-CD25 antibody [4]. Tacrolimus levels below this recommended range bear the risk of graft rejection, whereas levels above this range result in increased toxicity (e.g. nephrotoxicity, diabetes, tremor, hypertension) and increased susceptibility to opportunistic infections and malignancies [5].

Both Prograf® and Advagraf™ exhibit significant inter- and intra-individual variability in absorption owing to interactions with food and concomitant medications; also functional polymorphisms in the cytochrome P-450 system cause inconsistencies. In addition, both Prograf® and Advagraf™ exhibit a rather low bioavailability due to poor water solubility and pre-systemic gastrointestinal metabolism [6, 7]. As a result of this variability, standard dosing based on body weight is not an accurate predictor of drug exposure, and regular assessment of tacrolimus blood trough level concentrations is essential to measure effective drug exposure [8]. Currently, life-long monitoring of tacrolimus whole blood trough levels is required for all transplant patients [9].

Transplant recipients also typically require an array of concomitant medications for comorbidities, which means that interaction and tolerability profiles may cause issues. In addition, the intake schedule of many different medications may not easily be integrated into the patients’ daily life, which increases the risk of low patient compliance. As non-compliance with immunosuppressant dosing can result in graft rejection and failure, the once daily formulation of tacrolimus, Advagraf™, was designed to reduce the daily pill burden compared to Prograf® (taken twice daily). However, this potential benefit of Advagraf™ is counterbalanced by delayed achievement of therapeutic trough levels after transplantation and the need for an up to 50% higher dosage to maintain trough levels similar to Prograf® [10], therefore jeopardising tolerability.

A new once-daily formulation of tacrolimus, Envarsus®, was approved in 2014 by the European Medicines Agency (EMA) for the prophylaxis of rejection in kidney or liver allograft recipients and treatment of rejection resistant to other immunosuppressants [11]. Envarsus® is a prolonged-release formulation of tacrolimus developed using MeltDose™ drug-delivery technology, which increases the bioavailability of poorly water-soluble compounds via solid formulation at molecular state. Improvement in the bioavailability of Envarsus®, which allows once-daily administration, results in lower inter- and intra-patient variability of drug absorption with reduced peak-to-trough fluctuation and earlier achievement of a stable tacrolimus profile, as demonstrated in healthy volunteers [12]. In phase III studies using stable, de novo kidney transplant patients, Envarsus® has proven to be non-inferior to twice-daily tacrolimus in terms of treatment failure, a composite trial endpoint of death, graft failure, acute rejection or lost-to-follow-up [13, 14]. Additional potential benefits of Envarsus® are reduced pill burden and diminished peak-related toxicities such as tremor [15].

## Rationale

To characterise the metabolic profile of patients, several research groups have presented the calculation of the ratio between concentration in the blood and the drug dosage (C/D ratio) as a simple, practical and cost-neutral method easily applied during daily clinical practice, since trough level measurement is a necessary and routine part of therapeutic drug monitoring [16, 17]. A high C/D ratio indicates a slow rate of tacrolimus metabolism (i.e. lower doses of drug sufficient to maintain therapeutic blood concentrations); a low C/D ratio indicates a high rate of metabolism (i.e. higher doses of drug needed to maintain therapeutic exposure). Elevated tacrolimus peak levels are postulated as a possible reason for impaired kidney function and CNI nephrotoxicity in both liver and kidney transplant patients with low C/D ratio [16, 18]. The improved pharmacokinetic profile of Envarsus® with significantly lower peak levels in comparison to Advagraf™ [19] might be beneficial for these patients. It is widely reported that switching kidney transplant recipients to Envarsus® elevates the C/D ratio [20], since lower drug doses are sufficient to maintain therapeutic trough levels with this galenic drug formulation. Data from observational studies show that a higher C/D ratio can also be achieved when using this drug in LTx recipients [21, 22]. Since bioavailability studies on Envarsus® in the context of LTx are less prevalent in the scientific literature compared to kidney transplantation, and no phase III or IV studies with Envarsus® have been conducted in de novo LTx recipients, the EnGraft Study is designed to compare the bioavailability and practicability (handling) of two once-daily tacrolimus formulations Envarsus® versus Advagraf™ in de novo LTx recipients over 12 weeks. The recently identified and postulated parameter C/D ratio as an estimate for tacrolimus bioavailability will be calculated at different time points and will contribute to the pharmacokinetic profile of patients. The primary objective of EnGraft is to show that Envarsus® confers a superior (higher) C/D ratio in LTx recipients after 12 weeks of therapy under the conditions of a prospective, controlled, randomised clinical trial.

Several studies have identified a relationship between C/D ratio and clinical outcomes in organ transplant recipients. There is strong evidence that a lower C/D ratio (i.e. faster tacrolimus metabolism) is associated with inferior kidney function [23], a higher risk for CNI-induced nephrotoxicity [24] and greater susceptibility to BKV infection [25]. Conversely, studies in kidney transplantation have demonstrated that a higher C/D ratio (i.e. slower tacrolimus metabolism) is linked to a reduction in neurotoxic side effects such as tremor, headache and insomnia [20]. Moreover, a recently published observational study in LTx [21] has shown that a higher C/D ratio is associated with improved renal function, as measured by estimated glomerular filtration rate (eGFR).

Accordingly, it should be possible to limit renal dysfunction and reduce other tacrolimus-related toxicities by using a drug formulation that improves bioavailability and increases the C/D ratio. Therefore, a secondary aim of the EnGraft study is to prospectively test whether an elevated C/D ratio is associated with improved clinical outcomes. This is especially relevant in a patient population that is particularly vulnerable to kidney damage. The widespread use of the MELD (Model for End-Stage Liver Disease) score in determining organ allocation means that most LTx recipients already have impaired renal function at LTx. Since renal impairment is a typical side effect of CNI therapy, these patients are sensitive to CNI-induced nephrotoxicity very early after transplantation. The ReSpECT Study has already shown that lowering CNI exposure early after LTx is associated with better long-term kidney function [26]. Since C/D ratio correlates positively with eGFR after LTx [18], the EnGraft study aims to show that an elevated C/D ratio in the early post-transplant period can protect and preserve renal function without compromising liver allograft survival.

Since C/D ratio may be an effective tool for identifying patients at higher risk of developing poorer long-term outcomes in terms of kidney function and CNI toxicity, this study incorporates a long-term follow-up phase. By using C/D ratio to characterise patients in terms of tacrolimus metabolism at 12 weeks post-transplant, it will be possible to evaluate whether the sub-groups of slow, intermediate and high metabolisers exhibit long-term clinical outcomes that correlate with their metabolic profile. This would support the hypothesis that the C/D ratio has a predictive value that, when calculated during the early stages after LTx, may help transplant clinicians to identify patients at risk of long-term complications and to individualise patient therapy accordingly.

Therefore, the EnGraft Study will follow patients for 3 years in total in order to assess long-term efficacy and safety outcomes and to see whether these outcomes correlate with the metabolic profile measured during the early post-transplant period.

Controlled, prospective, multicentre trials are now needed to test the predictive value of the tacrolimus C/D ratio. Whilst published literature regarding C/D ratio in LTx is encouraging, we are currently reliant on retrospective, single-centre studies using small and heterogeneous patient cohorts. There are also very few direct pharmacokinetic comparisons of the two once-daily tacrolimus formulations (Advagraf™ and Envarsus®). The EnGraft study is the first large, multicentre, randomised, controlled study in LTx to test Envarsus® using C/D ratio as the primary variable.

## Study design

EnGraft is a prospective, randomised, controlled, multicentre, open-label, two-arm, parallel-group, phase IV clinical trial to assess bioavailability and practicability of *En*varsus® compared with Adva*graf*™ in de novo liver *t*ransplant recipients (EnGraft).

Two hundred and sixty eight (268) patients at 15 LTx centres in Germany will be enrolled and randomised in a 1:1 ratio to two study arms. Patients in the test arm will be treated with Envarsus® (test) as first-line CNI in the immunosuppressive regimen. The control arm will treat patients with Advagraf™ (comparator) as first-line CNI. Trial participants will additionally receive all of the other treatments that comprise a standard, multi-drug, immunosuppressive regimen for LTx recipients, according to routine clinical practice in Germany.

Since this trial compares two commercially available medications with different pharmaceutical formulations (Envarsus® tablets versus Advagraf™ capsules), simple, cost-neutral treatment blinding is not possible. The trial is being conducted as an open-label study.

LTx will be performed prior to study entry, according to the local standard at participating trial centres. An optional run-in phase is available, in case patients cannot be randomised immediately after transplantation surgery (e.g. unable to swallow study medication). Patients may be enrolled up to 14 days after surgery.

The day of randomisation to EnGraft is defined as trial day 0. After a 12-week controlled treatment phase, patients enter a follow-up phase of 2 years and 9 months. The final study visit is scheduled for 3 years after randomisation.

The study design adheres to the principles outlined in ICH-GCP E6 (R2). All patients aged ≥ 18 years who meet the eligibility criteria and give informed consent will be allocated to the study. Those patients are supplied with patient information. For each trial participant, an authorised and delegated trial investigator must obtain written informed consent after sufficient time for reflection prior to conducting any trial-related procedures involving the subject. After consent is obtained, patients are randomised to the trial. The used patient information sheet and the informed consent are both ethically approved (Fig. 1).

**Fig. 1 Fig1:**
[figure not shown]
Study flowchart. Showing trial phases and treatment arms

## Objectives

### Primary endpoint

All time points for study endpoints are measured relative to patient randomisation (day 0). The primary variable is the C/D ratio measured at 12 weeks. C/D ratio is being measured in this study as a surrogate for tacrolimus bioavailability (i.e. systemic exposure per mg of drug) and will be calculated according to the formula in Fig. 2.

**Fig. 2 Fig2:**

Calculation of C/D ratio. In this formula, “C” represents the trough level measured in a blood sample collected immediately prior to drug dosing on the day of a trial visit (*t*_0_) and “D” denotes the daily dose taken by the patient on the day prior to the visit (*t*_-1_)

A centralised measurement of the 12-week tacrolimus blood trough level at the University Hospital Regensburg will be used to calculate C/D ratio for the primary endpoint.

During the controlled treatment phase (first 12 weeks post-randomisation), tacrolimus should be dosed by the investigator to reach and maintain whole blood trough concentrations within the general reference range of 3–12 ng/ml. For every randomised patient, a narrower target range (with an interval of 3 ng/ml) within the wider reference range of 3–12 ng/ml is to be defined at all times and continually reviewed/revised based on clinical circumstances. The first target range is to be set prospectively by the investigator and documented in the eCRF at baseline to enable analysis of the pharmacokinetic endpoints. Since the frequency of trough level measurement directly influences pharmacokinetic endpoints, each trial centre aims to follow the minimum schedule of trough level measurement outlined in Fig. 3.

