## Interventions

### Randomisation

A dynamic allocation technique will be used for randomisation of patients fulfilling the trial eligibility criteria in a 1:1 ratio to one of two treatment arms: Envarsus® tablets (test IMP) or Advagraf™ capsules (comparator IMP). Pre-treatment with immediate-release tacrolimus (Yes/No), as well as trial site, will be used as stratification factors in the treatment allocation to minimise sources of treatment bias. The first stratification factor (study centre) will minimise systematic treatment bias at the study centre level and reduce the influence of inter-centre variability. The second stratification factor (pre-treatment with immediate-release tacrolimus) will minimise treatment bias at the level of the individual patient, since patients treated with Prograf® during the run-in phase can be expected to develop stable trough levels after randomisation more rapidly than patients who do not receive Prograf® prior to commencing IMP. Balancing the treatment arms with respect to this factor allows fair and unbiased evaluation of the secondary pharmacokinetic endpoints that evaluate the ease with which the first target trough level is achieved.

The allocation algorithm is programmed into a randomisation module in the trial database. Study investigators at the participating trial sites have access to the randomisation module via the online trial database and randomise using this central tool. It is vital that randomisation is performed as soon as possible after eligibility has been confirmed and no later than 14 days after transplantation surgery; enrolment after this time period is not allowed.

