### Visit 1—Baseline

At the baseline visit (visit 1), patients are randomised and baseline characteristics are measured. The date of the baseline visit is designated as trial “day 0” and must occur no later than 14 days after transplantation surgery.

In case the run-in phase is skipped, all screening procedures must be performed at the baseline visit prior to randomisation. Randomisation may take place only after all eligibility criteria have been checked and fulfilled.

The following baseline procedures/data will be performed/collected (the applicable panel of assessments is displayed in Fig. 4):Randomisation, dispensing of assigned IMP, explaining practicalities of drug administration to the patientPatient characteristics, including demographicsPast medical historyDonor and transplantation dataPhysical examination, including body weight12-lead ECGVital signs: blood pressure, pulse rate, body temperatureBlood sampling for clinical tests:◦ Haematology, serum biochemistry, including calculation of eGFR◦ Blood coagulation screen◦ Virology status: CMV, EBV, HCV, HBV◦ Tacrolimus trough level (if immediate-release tacrolimus given prior to randomisation)Urine sampling for clinical urine analysisReview and documentation of concomitant medication that interacts with IMP or is prohibited per protocol

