### Secondary endpoints

All secondary variables will be analysed by treatment group using descriptive statistical methods. Secondary efficacy variables for the controlled treatment phase may be analysed between the two groups using two-sided testing with nominal significance level *α* = 0.05 and are to be interpreted in a strictly exploratory sense. If appropriate, two-sided 95% confidence intervals will be provided.

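### The first target trough range, the yardstick for two exploratory secondary endpoints, is set by the unblinded randomising investigator, and the text does not require this before allocation is known

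*Protocol article*

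**What the plan says.** The Study design section states: "The trial is being conducted as an open-label study". Under Randomisation, the person who obtains the allocation is the site investigator: "Study investigators at the participating trial sites have access to the randomisation module via the online trial database and randomise using this central tool". This happens at day 0: "At the baseline visit (visit 1), patients are randomised and baseline characteristics are measured" (Visit 1—Baseline).

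The text under Fig. 2 gives the same role the choice of target: "For every randomised patient, a narrower target range (with an interval of 3 ng/ml) within the wider reference range of 3–12 ng/ml". Later changes to the range in the light of the patient's course are allowed. On timing of the first one, the text says: "The first target range is to be set prospectively by the investigator and documented in the eCRF at baseline to enable analysis".

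The Selected secondary endpoints section uses this first range twice. One endpoint is the number of days until it is reached, dated from the first of two consecutive in-range readings. The other is the number of readings above and below it.

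The safeguard named for endpoints of this kind is stratification on immediate-release tacrolimus pre-treatment: "Balancing the treatment arms with respect to this factor allows fair and unbiased evaluation of the secondary pharmacokinetic endpoints" (Randomisation, repeated in the Discussion). The statistical section on secondary endpoints plans descriptive analysis throughout and says that any tests of secondary efficacy variables "are to be interpreted in a strictly exploratory sense".

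**The concern.** A yardstick that is specific to each patient is safe in a randomised comparison only if its placement cannot depend on the arm. Here one person may learn the allocation and then place the yardstick, with a free choice of lower limit from 3 to 9 ng/ml.

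Expectations about the two products are strong in the article itself. The Background describes delayed achievement of therapeutic troughs with Advagraf, and the Discussion cites faster achievement with Envarsus. An investigator who shares that view could, without intending to, choose different ranges in the two arms. An arm difference in time to target or in out-of-range counts would then partly reflect the choice of range and not only the formulation.

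The time endpoint is one of three secondary endpoints named in the abstract, and practicability is part of the trial's title, so readers are likely to look at these results.

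**Working it through.** **Order of events.** Four statements in the protocol article bear on whether the range precedes allocation.

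1. The range is set prospectively (text under Fig. 2). This places it before the readings it will be used to judge. It does not place it before randomisation.
2. It is documented at baseline. Baseline is also the randomisation visit, so this does not settle the order.
3. It is defined for randomised patients. If anything, this suggests that allocation has already happened.
4. The list of procedures under Visit 1—Baseline starts with randomisation and dispensing. This is not evidence either way. The list is not chronological (demographics, history and donor data come after dispensing), and it does not mention the target range.

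The order is therefore left open.

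**What the stated safeguard does.** Stratified allocation balances the arms on pre-treatment and site. It acts before allocation is known and cannot govern a choice made afterwards. For biopsy-proven rejection, by contrast, the article guards against detection bias with a blinded central reading.

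**Possible size.** The plan gives no figure for this point, and its sample-size figures concern the C/D ratio only. All trough values below are assumptions.

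*Single reading, troughs unaffected by the range.* Assume troughs are normal with mean 7 and SD 3 ng/ml in both arms. The chance of being in a range from L to L+3 is Φ((L+3−7)/3) − Φ((L−7)/3).
- Range 6–9: Φ(0.667) − Φ(−0.333) = 0.7475 − 0.3694 = 0.378
- Range 8–11: Φ(1.333) − Φ(0.333) = 0.9088 − 0.6306 = 0.278
- Gap: 10.0 percentage points

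The gap depends on the assumed mean. At mean 6 it is 0.341 − 0.205, or 13.7 points (from unrounded values). At mean 8 it is 0.378 − 0.341 = 3.7 points. At mean 9 it reverses, 0.341 − 0.378 = −3.7 points.

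*Two consecutive readings.* For one pair of independent readings at mean 7, 0.378² − 0.278² = 0.143 − 0.077, about 6.6 points. The absolute gap for a single pair is smaller than for one reading, although the ratio is larger.

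*Troughs that follow the range.* Doses are adjusted toward the range, so troughs should move with it. Take the arm with range 8–11:
- Mean moves 1 ng/ml, to 8: Φ(1) − Φ(0) = 0.341, gap 0.378 − 0.341 = 3.7 points
- Mean moves the full 2 ng/ml, to 9: Φ(0.667) − Φ(−0.333) = 0.378, gap zero

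*Counts over repeated readings.* A simulation used identical, fixed troughs in both arms: mean 6, 7 or 8, between-patient SD 1.5, within-patient SD 2, 12 readings and 134 patients per arm. One arm had range 6–9 and the other a range shifted down.
- Shift of 0.5 ng/ml: mean below-range count changes by about 0.7 to 1.0 per patient, with nominal p<0.05 in about 60–69% of trials
- Shift of 1 ng/ml: change of about 1.2 to 1.9, with nominal p<0.05 in about 99–100% of trials
- Two consecutive in-range readings among the first five, shift of 1 ng/ml: 42% to 51% at mean 6, 51% to 50% at mean 7, 51% to 42% at mean 8

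The below-range count is thus sensitive to placement when troughs are fixed. For the time endpoint even the direction depends on the mean. None of these fixed-trough figures allows for dosing toward the range, so none estimates the bias in this trial.

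**The case against.** The text shown is a journal article. The full protocol and the assessment schedule in Fig. 4 are not shown, and the order of eCRF fields is the kind of detail an article may leave to them. The range must be set prospectively, and the endpoints use the first one, so later revisions cannot fit the yardstick to observed troughs. Only two of the 14 listed secondary endpoints use it, and they are exploratory. A fixed check also exists: the proportion of patients below, within or above the standard reference range at 1, 2, 4 and 12 weeks.

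Most of this stands, and it limits the weight of the point. It does not remove the point, because the article goes beyond silence. It describes the procedure, states its analytic purpose, and claims a fair and unbiased evaluation on the strength of a safeguard that cannot act on placement. Protection against retrofitting to later readings is also not protection against knowledge of the arm.

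A reader might infer that the endpoints are biased, or that the trial's main result is at risk. The documents support neither. They contain no data on where ranges are placed in each arm, they do not call these endpoints the main ones, and the C/D ratio at 12 weeks is calculated from a centrally measured trough and the previous day's dose without reference to the range.

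**Conclusion.** The point holds as a limited design weakness: independence of the first target range from allocation is not secured, and two exploratory endpoints rest on it. What is established is an open order of events, not an actual difference between arms.

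The effect cannot be sized from the documents. The 10-point illustration rests on an assumed mean of 7 and SD of 3 ng/ml, a systematic 2 ng/ml difference in placement, and troughs that do not respond to it. Relaxing the last assumption takes the gap to 3.7 points or to zero. The claim that requiring two consecutive readings must enlarge the effect is also not supported. The primary test, its type I error and the sample size are untouched.

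**What to change.** - **Remaining patients:** make the first target range a mandatory eCRF entry that is saved before the randomisation module releases the allocation, and state this order in the protocol.
- **All patients:** tabulate the first range by arm. Where entry times exist, check whether the entry preceded allocation.
- **If the ranges are alike by arm:** the concern is largely settled.
- **If they differ:** report the two endpoints with a caveat and rely on the proportions against the fixed reference range. A range chosen after allocation is a post-randomisation variable, so adjusting for it is a sensitivity analysis only and not a cure.

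The cost is a minor eCRF change, a note to sites and one extra table. The eCRF change may reach few patients, because recruitment was estimated to end in June 2023 and the article appeared in May 2023. The table by arm is useful whatever the recruitment status. No change to the ranges or to dosing is implied.
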